# Food 4 Health - He Oranga Kai: Assessing the efficacy, acceptability and economic implications of *Lactobacillus rhamnosus* HN001 and β-glucan to improve glycated haemoglobin, metabolic health, and general well-being in adults with pre-diabetes: study protocol for a 2 × 2 factorial design, parallel group, placebo-controlled randomized controlled trial, with embedded qualitative study and economic analysis

**DOI:** 10.1186/s13063-019-3553-7

**Published:** 2019-07-29

**Keywords:** *Lactobacillus rhamnosus* HN001, Beta-glucan, Pre-diabetes, Probiotic, Prebiotic, DASS21, SF36, Acceptability, Economic analysis, Efficacy

## Abstract

**Background:**

The rates of pre-diabetes and type 2 diabetes mellitus are increasing worldwide, producing significant burdens for individuals, families, and healthcare systems. In New Zealand, type 2 diabetes mellitus and pre-diabetes disproportionally affect Māori, Pacific, and South Asian peoples. This research evaluates the efficacy, acceptability, and economic impact of a probiotic capsule and a prebiotic cereal intervention in adults with pre-diabetes on metabolic and mental health and well-being outcomes.

**Methods:**

Eligible adults (*n* = 152) aged 18–80 years with pre-diabetes (glycated haemoglobin 41–49 mmol/mol) will be enrolled in a 2 × 2 factorial design, randomised, parallel-group, placebo-controlled trial. Computer-generated block randomization will be performed independently. Interventions are capsulated *Lactobacillus rhamnosus* HN001 (6 × 10^9^ colony-forming units/day) (A) and cereal containing 4 g β-glucan (B), placebo capsules (O_1_), and calorie-matched control cereal (O_2_). Eligible participants will receive 6 months intervention in the following groups: AB, AO_1_, BO_2_, and O_1_O_2_. The primary outcome is glycated haemoglobin after 6 months. Follow-up at 9 months will assess the durability of response. Secondary outcomes are glycated haemoglobin after 3 and 9 months, fasting glucose, insulin resistance, blood pressure, body weight, body mass index, and blood lipid levels. General well-being and quality of life will be measured by the Short-Form Health Survey 36 and Depression Anxiety Stress Scale 21 at 6 and 9 months. Outcome assessors will be blind to capsule allocation. An accompanying qualitative study will include 24 face-to-face semistructured interviews with an ethnically balanced sample from the β-glucan arms at 2 months, participant focus groups at 6 months, and three health professional focus groups. These will explore how interventions are adopted, their acceptability, and elicit factors that may support the uptake of interventions. A simulation model of the pre-diabetic New Zealand population will be used to estimate the likely impact in quality-adjusted life years and health system costs of the interventions if rolled out in New Zealand.

**Discussion:**

This study will examine the efficacy of interventions in a population with pre-diabetes. Qualitative components provide rich description of views on the interventions. When combined with the economic analysis, the study will provide insights into how to translate the interventions into practice.

**Trial registration:**

Australian New Zealand Clinical Trials Registry, ACTRN12617000990325. Prospectively registered on 10 July 2017.

**Electronic supplementary material:**

The online version of this article (10.1186/s13063-019-3553-7) contains supplementary material, which is available to authorized users.

## Background

The prevalence of diabetes almost doubled worldwide between 1980 and 2016 [1]. This was predominantly driven by a rise in the rates of type 2 diabetes mellitus (T2DM) and pre-diabetes, which are associated with increasing rates of overweight or obesity [1]. In New Zealand, diabetes is one of the fastest growing long-term health conditions with an estimated increase of 7% per annum [2]. In addition, there are significant ethnic inequalities in the rates of diagnosed T2DM (2012/2013 data), with rates of 7% for Māori people, 13% for Pacific people, and 7% for Asian people, compared with 5.8% in the overall population [3], and pre-diabetes (2008/2009 data), with rates of 30% for Māori people and 30% for Pacific people, compared with 26% overall [4].

Pre-diabetes is an intermediate phase in the development of T2DM when glucose concentrations are between normal levels and those levels that define clinical diabetes [5]. Up to 70% of individuals with pre-diabetes will eventually develop T2DM [6]. Reversion to normal glucose levels, even if it is only transient, is associated with about half the risk for T2DM [7].

Diabetes is extremely costly to individuals, the healthcare system, and society as a whole [1, 2]. Healthcare costs are three times higher for an individual with diabetes compared with those for individuals without diabetes [2]. In addition, costs through loss of productivity exceed the healthcare costs [2].

Diabetes is associated with significant morbidities such as peripheral vascular disease, adult-onset blindness, renal failure, stroke, and cardiovascular disease (CVD) [8]. Depression is present at nearly double the normal rate in individuals with T2DM [9]. Lifestyle interventions, including dietary modification, exercise, and weight loss, are currently the main interventions used to reduce the risk of progression from pre-diabetes to T2DM [10]. However, these interventions are costly to implement and difficult to sustain. Additional effective measures, which are cost-effective and easy to implement on a broad scale, are required. To reduce health inequalities, such measures need to be acceptable and accessible to the groups at the highest risk of developing diabetes.

### Gut microbiota and health

Gut microbiota respond to environmental changes and moderate human physiology in multiple ways, which are not encoded for in the human genome [11, 12]. Dysbiosis (imbalance of microbial species in the body) has been associated with many health conditions including obesity, metabolic syndrome, non-alcoholic fatty liver disease, diabetes, and depression [13–15]. Therefore, the deliberate modulation of gut microbiota opens new possibilities in the search for ways to reduce the development of diabetes, CVD, and depression.

### Probiotics

Probiotics are defined by the World Health Organization as “live microorganisms which when administered in adequate amounts confer a health benefit to the consumer” [16]. Many different organisms are recognised as probiotics. Crucially, the health effects of probiotics are specific to the type, species, and strain of the probiotic used [17], and may be dose-dependent [18].

In a randomized controlled trial [19] we found that supplementation with the probiotic *Lactobacillus rhamnosus* HN001 (HN001) (6 × 10^9^ colony-forming units (cfu) daily) in pregnant women from 14 to 16 weeks gestation reduced the incidence of gestational diabetes, using the local New Zealand criteria for gestational diabetes, from 6.5% in the placebo group to 2.1% in the probiotic group (absolute risk difference 4.4%, *P* = 0.03) [20]. Notably this result was achieved without any other dietary or lifestyle modification. Post-natal depression scores and anxiety prevalence were also reduced in the probiotic arm of this study: the Edinburgh postnatal depression scale score for HN001, mean = 7.7 (standard deviation (SD) = 5.4) compared with 9.0 (SD 6.0) in the placebo group (*P* = 0.037); and anxiety present in 15.6% compared with 29.4% in the placebo group (adjusted *P* = 0.002) [21]. Our research extends this work to study the effect of the same probiotic in those with pre-diabetes, but with the addition of prebiotic/fibre intervention to optimize the potential health benefits.

### Prebiotics and fibre

Prebiotics are nondigestible high-fibre food components that are selectively fermented by particular members of the gut microbiota providing benefits to the health of the host [22]. Both soluble and insoluble fibre intake are important for prevention and treatment of T2DM, obesity, CVD, and hyperlipidaemia [23, 24].

Specifically, β-glucans are soluble polysaccharide prebiotics with a high molecular weight and are present in a range of noncereal and cereal foods, including oats and barley [25, 26]. The health properties of β-glucans are well documented [23, 26–31]. A 2018 meta-analysis of oat β-glucan (median dose 3.5 g/day) including data from 58 trials (*n* = 3974) found modest reductions in low-density lipoprotein (LDL; 0.19 mmol/l), non-high-density lipoprotein cholesterol (non HDL-C; 20 mmol/l), and apolipoprotein B (0.03 g/l) [32]. The European Food Safety Authority (EFSA) has endorsed claims that 4 g β-glucan significantly reduces blood glucose after meals, and 3 g/day decreases blood cholesterol [33]. However, to our knowledge there is little published evidence of the long-term effects of β-glucan and in particular whether these effects result in achievement and long-term maintenance of normal blood glucose concentrations, which is fundamental in decreasing the risk of developing T2DM.

Based on the above evidence of benefits from oat-derived β-glucan, in this research we will pair β-glucan with HN001. Furthermore, in vitro research indicates that β-glucan supports the growth of HN001 [34]. We contend that, in contrast to a probiotic-only intervention, this modification will most benefit metabolic and mental health outcomes.

In summary, diabetes is a significant and growing challenge worldwide with multiple social, economic, and health implications. Novel treatments are needed to help reduce the risk of pre-diabetes progressing to T2DM and in turn reduce the risk of the complications of diabetes. Building on our previous research, the Food 4 Health study: He Oranga Kai^1^ (F4H) utilises *L. rhamnosus* HN001 with the addition of the prebiotic β-glucan to quantitatively evaluate the health effects in adults with pre-diabetes. An in-depth understanding of the experiences of study participants in taking the study interventions, including their acceptability, and how these interventions are used by a range of ethnic groups including those most at risk of diabetes in New Zealand will be obtained through qualitative research methods. The study will seek health professional views on how to implement the intervention in practice. This, in combination with results from an economic analysis, will provide insights into how to translate the interventions into practice.

### Overarching aims

The overall goals of this work are: 1) to investigate the metabolic and other physical and psychological health effects of the single or combined use of daily HN001 probiotic and cereal enriched with 4 g β-glucan for 6 months in adults with pre-diabetes and the persistence of any health effects for a further 3 months after stopping the interventions; 2) to ascertain the acceptability of the study interventions, how they are adopted into participant’s lives, and develop a pathway to implementation; and 3) to establish the cost effectiveness of the intervention at the population level.

## Methods/design

### Randomized controlled trial design and hypotheses

This is a 2 × 2 factorial design, randomised, parallel-group, placebo-controlled trial in 152 adults with pre-diabetes designed to test the hypotheses that the administration of 6 months of the probiotic HN001 (6 × 10^9^ cfu) either alone or in combination with a cereal enriched with 4 g β-glucan to adults with pre-diabetes for 6 months will reduce glycated haemoglobin (HbA1c). The allocation ratio to groups will be 1:1:1:1. The design is to test the superiority of HN001 with or without 4 g β-glucan over placebo.

### Randomization and blinding

Randomization will be performed independently by Fonterra Co-Operative Ltd, using Microsoft Excel and a computer-generated random number list according to procedures explained by Kim and Shin [35]. Randomization will be performed in blocks of eight and not stratified; however, covariates will be collected and an important selection of these will be used in a sensitivity analysis.

The study is double-blinded for study capsules and only the study statistician will be unblinded after data analysis of the 6-month primary outcome. Outcome assessors and all participants will remain blinded to capsule allocation until all 9-month follow-up data are collected. Due to the obvious difference in cereals the study is not blinded for cereals; however, participants will not be informed of the full rationale for cereal choices, the full contents of cereal packages, or which cereal is considered the intervention and which is the control until after all participants have completed the study.

Fonterra Co-Operative Ltd will share the study cereal allocation codes with the study centre, while capsule allocations will remain double-blinded until data are analysed.

Staff will allocate the next study number in consecutive sequence to those eligible at the commencement of the enrolment visit. The type of cereal allocated will only be revealed to the participant at the time the relevant intervention is dispensed after baseline measures are collected.

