### Sample size

There are few published studies reporting HbA1c change following lifestyle or pharmaceutical intervention in pre-diabetes. For example, a trial in those with pre-diabetes by Defronzo et al. [53] on a drug intervention using pioglitazone reported a point estimate of the reduction in HbA1c of 0.24% (2.6 mmol/mol) relative to placebo. In T2DM a clinically important difference with drug interventions is 5 mmol/mol. Past research reports an SD for HbA1c in similar clinical samples to those with pre-diabetes of between 4 and 6 mmol/mol [54]. Based on the larger of these SDs, a sample size of 32 in each main effects arm has 90% power to detect a 5 mmol/mol reduction with a type I error rate of 5%. Accounting for 25% drop-out, a total sample size of 88 is needed (22 in each factorial combination). The power to detect differences is likely to be improved using baseline HbA1c as a continuous covariate. However, an uncertainty for this study is whether the minimal clinically important difference for reduction of HbA1c in the setting of pre-diabetes should be anticipated to be closer to that seen in the pioglitazone study (increasing the required sample size), and that the SD for the HbA1c is likely to be smaller in pre-diabetes than in T2DM (decreasing the required sample size). For 80% power to detect a difference of 2.6 mmol/mol with an SD of 4 and 25% drop-out, a total recruitment of 92 is needed, and for 90% power *n* = 136. For a difference of 3.8 mmol/mol, half-way between the two values, and the larger SD of 6, a total sample size of 152 participants with 38 in each factorial combination will be recruited for this study.

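### Fixed blocks of eight on one consecutive list, with the cereal open, leave about 20% of cereal assignments deducible by anyone who knows the block size and keeps a tally, even if the cereal codes are withheld

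*Protocol article*

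**What the plan says.** All the elements are in the protocol article.

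- **List.** Randomization and blinding: "Randomization will be performed in blocks of eight and not stratified". One block size is given and there is one running list.
- **Ratio.** Randomized controlled trial design and hypotheses: "The allocation ratio to groups will be 1:1:1:1".
- **Number.** Sample size: "a total sample size of 152 participants with 38 in each factorial combination will be recruited for this study".
- **Order of use.** Randomization and blinding: "Staff will allocate the next study number in consecutive sequence to those eligible at the commencement of the enrolment visit".
- **Visibility of the cereal.** Same section: "Due to the obvious difference in cereals the study is not blinded for cereals". It adds that "The type of cereal allocated will only be revealed to the participant at the time the relevant intervention is dispensed after baseline measures are collected". That sentence limits what the participant learns. It does not address what staff can infer from earlier dispensings.
- **Codes.** Same section: "Fonterra Co-Operative Ltd will share the study cereal allocation codes with the study centre", while "capsule allocations will remain double-blinded until data are analysed". The article does not say when the cereal codes are shared, or with whom at the centre.

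**The concern.** A block is a promise that the tally returns to balance at a known point. When assignments are masked, nobody at the site can use that promise. Here one of the two randomized factors can be seen at every dispensing, and numbers are issued in order, so blocks end at numbers 8, 16, 24 and so on. Once four of one cereal have gone out within a block, the rest of that block is known before the next participant is enrolled.

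At stake is allocation concealment for the cereal main effect, one of the two factors in the primary ANCOVA of 6-month HbA1c. The exclusion list ends with a judgement item that lets investigators turn away someone over expected compliance or safety. Someone who could foresee the next cereal could apply that judgement unevenly, knowingly or not. Adjusting for baseline HbA1c removes only the part of such selection that baseline HbA1c captures.

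**Working it through.** The article gives no figure for predictability, so there is none to reproduce.

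**Inputs from the article.** Block size 8; ratio 1:1:1:1; total 152; consecutive numbering; cereal open; SD 6 mmol/mol, 25% drop-out and a target difference of 3.8 mmol/mol (Sample size).

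**Inputs assumed.** The observer knows the block size and the order of earlier cereals. ±δ is the shift in expected 6-month HbA1c of a steered participant, beyond what baseline HbA1c explains. The documents give no value for δ, so a range is shown.

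**Block content.** Two per group gives 2 + 2 = 4 active and 4 control cereals per block. The 2520 orderings of the four groups reduce to C(8,4) = 70 cereal sequences, each arising from 36 orderings, so the 70 are equally likely. 152/8 = 19 complete blocks.

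**Certain assignments.** With m = 4 of each cereal, the expected number deducible per block is 2m/(m+1) = 8/5 = 1.6, a share of 1/(m+1) = 20%. Over 19 blocks, 19 × 1.6 = 30.4 of 152. By position:

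| Position in block | 1–4 | 5 | 6 | 7 | 8 |
|---|---|---|---|---|---|
| Probability it is certain | 0 | 2.9% | 14.3% | 42.9% | 100% |

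These sum to 1.6.

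**Best guess (the cereal used less so far in the block).** Expected correct = m + (4^m/C(2m,m) − 1)/2 = 4 + (256/70 − 1)/2 = 5.33 of 8 = 66.6%, against 50% under full concealment.

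**Alternatives.**

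| Scheme | Certain | Best guess right |
|---|---|---|
| Fixed blocks of 4 | 33.3% | 70.8% |
| Fixed blocks of 8 (plan) | 20.0% | 66.6% |
| Fixed blocks of 16 | 11.1% | 62.8% |
| One permuted list of 152 | 152/77 = 2.0 assignments (1.3%) | 83.2/152 = 54.8% |

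Small random sizes (4, 8 or 12) largely remove certainty but, by simulation, leave the best guess right about 66% of the time.

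**Possible bias in the cereal contrast.**

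- *Acting on certain assignments only.* The active arm's mean moves by 0.20δ and the control arm's by −0.20δ, so the bias is 2 × 0.20 × δ = 0.4δ.
- *Acting on every guess.* The excess of right over wrong guesses is 0.666 − 0.334 = 0.332, so the bias is 2 × 0.332 × δ, about 0.66δ. Simulation gives about 0.65δ.

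**False rejection of a true null at 5%.** Retained per cereal arm: 152 × 0.75/2 = 57. SE = 6 × √(2/57) = 1.12 mmol/mol. This is an unadjusted comparison, used for scale only. The first two result columns use 0.4δ and the normal approximation; the last is simulated.

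| δ (mmol/mol) | Bias, certain only | Rejection, certain only | Rejection, every guess |
|---|---|---|---|
| 1 | 0.4 | 6.5% | about 8% |
| 2 | 0.8 | 11% | about 20% |
| 3 | 1.2 | 19% | about 37% |

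At δ = 2 the certain-only bias is 0.8/3.8 = 21% of the target difference.

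**The case against.** The case against has real force.

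- **The shared codes may dominate.** If enrolling staff hold the cereal codes in advance, every cereal assignment is foreseeable and the block size is irrelevant. This stands: changing the blocks alone would then achieve nothing. It does not remove the point, because withholding the codes alone leaves the 20%. A reader might infer that all cereal assignments are in fact known beforehand. The article does not say when the codes are shared or who at the centre sees them, so it does not support that.
- **Knowledge of the block size is assumed.** This stands. The list is generated independently of the site. The article appeared in July 2019, after the approximate completion date of April 2019 that it gives, so publication itself is unlikely to have informed enrolment. Whether field staff were told the block size may be settled in the full protocol, which is not shown.
- **The larger error rates are an upper case.** This stands. The 8%, 20% and 37% require steering on every guess. A ±δ shift is a 2δ swing between favoured and disfavoured participants: at δ = 2 that is 4 mmol/mol, more than the 3.8 target. The primary analysis adjusts for baseline HbA1c, and further planned analyses adjust for BMI, exercise and energy intake, so the δ that remains may be small.
- **The route for selection is narrow.** Largely true. Eligibility rests mostly on listed criteria and a measured HbA1c, a catch-all exclusion is routine, and nothing says staff choose the order of booking.
- **Blocks of eight have a purpose.** They hold the groups balanced over calendar time and if recruitment stops early. With a single unstratified list that benefit is modest, but it is not nil.

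**Conclusion.** The structural point holds. The 20% certain and 66.6% guessable figures are exact consequences of the stated block size, ratio and open cereal. They are conditional on someone at enrolment knowing the block size and tallying dispensings, and they describe what remains if the codes are withheld.

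The bias is potential. About 0.4δ is the figure that matches the certain assignments; about 0.65δ is the upper case. Both depend on an assumed δ with no source in the documents. A reader might infer that selection occurred, or that the trial's false-positive rate is 20% or more. Nothing in the article shows either. Nor does the point reach the HN001 comparison, since capsule allocation stays masked.

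This is a worthwhile, inexpensive improvement to concealment for the cereal main effect, and not a flaw that invalidates the design.

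**What to change.** In Randomization and blinding, make three changes together:

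1. Replace fixed blocks of eight with one randomly permuted list of 152 (38 per combination), or with large blocks of randomly varying size. Small varying sizes are a weaker choice, for the reason given in the working.
2. State that the block structure is kept from enrolling staff.
3. State that each cereal code is released only after that participant is irrevocably enrolled. Without this, the first change has no effect if the codes are held in advance.

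The article says recruitment began in February 2018, so this can apply only to numbers not yet allocated, and there may be none. For numbers already allocated, report who knew the block size and who held the cereal codes and when, and compare baseline characteristics by cereal and by position in block, where the later positions are the exposed ones.

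Cost: a few sentences and, if numbers remain, a regenerated remainder of the list from the existing holder, plus a procedure for releasing codes one at a time. The price is slightly less balance over calendar time, and a possible small imbalance between groups if recruitment stops short of 152.

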#### Study cereals

Cereals were chosen as the delivery method for the β-glucan prebiotic intervention to enable an adequate dose to be administered in the intervention cereal. In addition, cereals can be administered as a food in a range of formats to increase the variety of options for participants.

The active cereal contains 40 g Uncle Toby’s Flemings Rolled Oats (manufactured by Nestle Australia) and 8 g of OatWell® 28XF oatbran (supplied by DSM Nutritional Products Ltd, Switzerland) or 8 g SWEOAT Bran BG28 XF (the same product; supplied by Swedish Oat Fiber AB, Sweden) (www.sweoat.com). Total β-glucan dose is 4 g. Oatwell 28/SWEOAT Bran BG28 XF is a heat-treated extra-fine oatbran containing 28% high-viscosity-solubility and high-molecular-weight (> 2000 kDa) β-glucan.

The control cereal contains 35 g cornflakes (manufactured by Sanitarium Health and Wellbeing, Auckland, New Zealand) and 8 g non-dairy creamer (C35; manufactured by Shantou City Chenghai District Wenhui Food Co. Ltd, China).

Cornflakes and creamer were chosen as the control cereal as they are expected to have minimal prebiotic effect. Having a control cereal and powder enhances the study design by enabling some masking of which cereal contains the active interventions. Active and control ereals are calorie matched. See Additional file 1 for comparison of cereal nutritional values.

HealthPak Ltd, Penrose, Auckland, New Zealand, will pack the study cereals and supply them in single-serve daily portions. To ensure precise dosing, each individual daily serving contains two opaque packs, one containing the course-grained cereal (oats/cornflakes) and a smaller sachet containing the powder (β-glucan or non-dairy creamer) The two sachets which together constitute a daily serving of cereal are enclosed together in a clear outer package.

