#### Staff training

To ensure that high-quality and consistent data are collected, all field staff will be trained in the administration of study questionnaires and assessments of physical measures according to standard study protocols.

Field staff will instruct the participant on the completion of the SF36 using standard recommended procedures [42]. Anthropometric and blood pressure data will be collected using clearly defined protocols, standardized and calibrated equipment, and with duplicate readings and range checks to ensure data reliability. See Additional file 2 for equipment and protocols for anthropometric and blood pressure measures.

Staff trained in phlebotomy procedures will collect fasting blood according to a standardized protocol. After centrifuging, aliquots of serum or plasma will be stored at −80 °C until processed. Analysis will be performed in batches containing all of an individual’s samples to minimize measurement error due to batch variability. Those consenting to the collection of faecal samples will collect these samples in the 2–3 days prior to each study visit immediately after completing the 3-day food diary. See Additional file 5 for details on the blood and faecal sample collection and quality-control protocols.

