### Economic analysis

The aim of the economic analysis is to model the potential cost-effectiveness of the intervention if it were implemented in a wider New Zealand context. The change in HbA1c, BMI, blood pressure, and serum total cholesterol observed at 6-month follow-up in the randomized controlled trial will be used in the model as estimates of the effectiveness of the intervention. These changes in risk factors will be modelled through to a change in incidence of the relevant diseases and then onto changes in quality-adjusted life years (QALYs), costs or cost savings to the health system (in 2011 New Zealand dollars; NZ$) and incremental cost-effectiveness ratios which show the health system cost per QALY gained. A health system perspective will be used, and benefits and costs will be modelled using a lifetime horizon. Outputs will be discounted at 3%.

The intervention will be modelled using a multi-state life-table (MSLT) model populated with rich New Zealand health data. An existing MSLT model, which is parameterised for the whole of the New Zealand population [66, 67], will be re-parameterised to the New Zealand population with pre-diabetes using data from routinely collected administrative health data (Healthtracker and the Integrated Data Infrastructure) and the Adult Nutrition Survey 2008/2009. In order to estimate the difference in QALYs and health system costs between the model’s intervention and business-as-usual (BAU) comparator, the entire New Zealand population alive in 2011 will be simulated out until death.

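### Assessor blinding stops at the capsule, so field staff may know the cereal when they measure waist and, with less scope for bias, blood pressure and weight

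*Protocol article*

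**What the plan says.** **Scope of blinding.** The abstract states: "Outcome assessors will be blind to capsule allocation". The section on randomization and blinding repeats the same scope: "Outcome assessors and all participants will remain blinded to capsule allocation until all 9-month follow-up data are collected". On the other factor it says: "Due to the obvious difference in cereals the study is not blinded for cereals". The company that runs the randomization "will share the study cereal allocation codes with the study centre", and no limit on who there may see them is given. Participants are not told which cereal is the active one until everyone has finished.

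**Timing at enrolment.** The same section has staff allot the next study number at the start of the enrolment visit. The participant learns the cereal only after baseline measures. No matching protection is stated for staff.

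**Who measures.** Under staff training, "all field staff will be trained in the administration of study questionnaires and assessments of physical measures". No separate assessor role is described. The section on adherence has participants coached on fitting the cereal into their eating, and unused cereal returned and counted.

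**What is measured.** Table 1 lists blood pressure, weight, waist and BMI as secondary outcomes at 3 and 6 months. Blood pressure and weight use calibrated electronic equipment. Waist uses standard equipment and a protocol. The economic model takes as its effectiveness inputs "The change in HbA1c, BMI, blood pressure, and serum total cholesterol observed at 6-month follow-up".

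**The concern.** The reason given for the open cereal concerns the participant. It does not reach the person holding the tape, whose knowledge of the arm is a separate choice. By stating assessor blinding for the capsule alone, the protocol leaves one of its two randomized factors without protection against observer bias on every outcome that staff measure by hand or by device.

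An analysis plan cannot repair this afterwards. If measurers who expect the oat cereal to work read slightly lower in that arm, the difference appears as a β-glucan effect. For blood pressure and, through weight, BMI, it would also pass into the cost-effectiveness model.

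**Working it through.** The plan gives no figure on this point, so the main check is a reading of the passages together. The arithmetic afterwards is only an illustration.

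**1. Can the measurer know the cereal?**
- Codes: held at the study centre, access not limited (Randomization and blinding).
- Baseline: the study number, which maps to a cereal through the codes, exists before the measures are taken (same section).
- 3 and 6 months: field staff are trained for both questionnaires and physical measures (Staff training). Cereal is returned and counted, and is discussed at the 3-month visit (Adherence). A question at both visits asks about reduced doses of the corn or oats (Table 2).

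Nothing stated prevents the measurer from knowing. That each measurer does know is a strong inference, not a statement in the text.

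**2. Which outcomes are exposed?**

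| Outcome | How measured | Exposure to observer bias | Economic model input |
|---|---|---|---|
| HbA1c, glucose, insulin, lipids | laboratory | none from this source | HbA1c and total cholesterol |
| Waist | standard equipment, no electronic device stated | highest | no |
| Blood pressure | electronic | lower | yes |
| Weight, hence BMI | electronic | lower | BMI |

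**3. How much could a given bias matter?**

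Inputs from the Sample size section: 152 recruited and 25% drop-out. Per cereal arm: 152 × 0.75 / 2 = 57.

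Let b be an assumed systematic reading difference between cereal arms, in units of the outcome's SD as analysed (after baseline adjustment). With no true effect:

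- SE = √(2/57) = 0.187
- P(reject) = Φ(b/SE − 1.96) + Φ(−b/SE − 1.96)

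| b (SD) | P(reject) |
|---|---|
| 0 | 5.0% |
| 0.1 | 8.3% |
| 0.2 | 18.7% |
| 0.3 | 36.0% |

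In natural units, with assumed SDs, the SE is SD × √(2/57):
- Waist, SD 3, 4 or 5 cm: a 0.5 cm shift gives 14, 10 or 8%; a 1 cm shift gives 43, 27 or 19%.
- Systolic pressure, SD 8, 10 or 12 mmHg: a 1 mmHg shift gives 10, 8 or 7%; a 2 mmHg shift gives 27, 19 or 14%.

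The 43% is the extreme corner, with the largest shift and the smallest SD. The documents supply neither the shifts nor the SDs.

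**The case against.** **The open cereal is declared, with a reason and a partial safeguard.** This stands. It is a design weakness and not a contradiction.

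**The measures have safeguards.** Staff are trained, protocols are defined, equipment is calibrated, and readings are duplicated and range-checked. This stands in part. It limits random error and, with electronic devices, the observer's room to influence a reading. It does not remove a consistent lean by someone who knows the arm, above all for waist.

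**Baseline adjustment may absorb some of it.** If the same shift b occurs at baseline and follow-up, and the ANCOVA slope on baseline is β, the net bias is b(1 − β), which is small for a measure that tracks closely. This stands for a shift in the same direction at both visits. A shift at follow-up only is not reduced.

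**The order of measurement may be fixed in Additional file 2 or the full protocol.** It may, and its absence from the article is not the point. The article does state the scope of assessor blinding, and that scope is the capsule.

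**Masking would be fragile.** Participants know their cereal, and visits cover diet and cereal dose. This stands: masking would be incomplete.

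Two stronger readings should be set aside:
- A reader might infer from "each individual daily serving contains two opaque packs" that the packaging makes it feasible to blind staff. The section on study cereals links the packs to precise dosing, places them in a clear outer package and claims only partial masking of which cereal is active. The contents also differ in weight (40 g + 8 g against 35 g + 8 g). The packs do not establish feasibility.
- A reader might infer from the data monitoring section that someone outside the field team already holds the codes. It says only that a non-fieldworker would contact the code holder at the company if unblinding were needed.

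**Conclusion.** The concern holds in a limited form. The protocol restricts assessor blinding to the capsule, shares the cereal codes without a stated limit and allots the study number before baseline measures. This leaves avoidable observer bias in the β-glucan comparison for waist and, to a lesser degree, blood pressure and weight.

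A reader might take this to mean that the whole β-glucan comparison is compromised. The documents do not support that: HbA1c, the primary outcome, and all other laboratory outcomes are outside its reach. Nor does the most exposed measure, waist, feed the economic model; of the staff-measured outcomes, only blood pressure and BMI do.

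The size rests on two things the documents do not settle: that measurers in fact know the cereal, and how far that moves a reading. If the shift were 0.1 to 0.3 SD, the false-positive rate would be about 8–36% in place of 5%. With no shift, nothing is lost.

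**What to change.** In the section on randomization and blinding, extend assessor blinding to the cereal for waist, blood pressure and weight, as far as existing staff allow:

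1. At enrolment, take these measures before the study number is allotted.
2. Restrict the cereal codes to staff who dispense. Step 1 needs this too, because numbers run consecutively and a measurer holding the codes could look up the next one.
3. At 3 and 6 months, take these measures first, before cereal is returned, counted or discussed.
4. Ask participants not to mention their cereal while being measured.
5. Where staffing allows, use a measurer who has not coached that participant. A guaranteed separate assessor would need extra resources and is not asked for.

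Recruitment began in February 2018, with completion expected around April 2019 (Trial status), so many visits may already be done. For those, and wherever masking fails, report the β-glucan results for these outcomes as unblinded assessments, and say so where blood pressure and BMI enter the economic model. If the procedure changes part-way, record the date.

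Cost: a tighter visit order, some control of code access, and masking that will remain incomplete.
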